### **5.3.1 Control group**

Specialists in the hospitals with CTcue will be unaware of the patients functioning as controls during this study, since data for controls will be collected retrospectively. In the participating hospitals without access to CTcue, control patients will be gathered prospectively. The aim is that each participating hospital gathers a control group which will be compared with their intervention group.

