### 5.1.5 Sample size

We hypothesize that implementing the care pathway will reduce the mean ED-LOS with 10%. In a prospective study about the quality of Acute Care, by [name] (submitted for publication), the mean length of stay at the ED in the Maxima Medical Centre is three hours and twenty minutes (95% CI 3:00-3:40, SD=1.17). Assuming a normal distribution, a two sided test, power of 80% and a significance level ( $\alpha$ ) of 0.05, a minimum of 466 patients need to be included, 233 patients in both control and intervention group. We aim to include 300 patients in each group, with a estimated timeframe of one year. Each hospital will gather their own control-group before implementation of the care-pathway. A minimum number of control-patients will be established for each participating hospital, dependent of number of annual patient-visits at the Emergency Department.

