## 5.5 STATISTICAL ANALYSIS

Primary and secondary study parameters and endpoints are described in 'Study parameters/endpoints'. All statistical analyses will be performed with SPSS 24.0 for Windows (IBS, SPSS Statistics, Chicago, IL, USA). Descriptive statistics will be used for frequencies, percentages, means and standard deviations. Continuous variables will be analysed using independent t-tests, whereas the categorical data will be analysed by chi-square or Fisher's exact test. Median and interquartile ranges of non-normally distributed categorical and metric variables of the study will be

assessed using Mann-Whitey-U-test. Prevalence of the most frequent diagnosis (coded ICD-10) at discharge will be presented in percentages. HR and corresponding 95% confidence intervals will be calculated. Generalized Estimating Equations (GEEs) will be used, which adjust for observations made within the same hospitals being more alike. All tests will be performed using a significance level of  $\alpha = 0.05$ . A two-sided p-value  $< 0.05$  will be considered significant.

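### The methods listed for ED-LOS in Protocol 5.5 do not secure the within-hospital comparison that Protocol 5.3.1 intends

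*Protocol*

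**What the plan says.** ED-LOS is one of the two main endpoints (Protocol 1 and 3). Three sections bear on how it is compared.

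- **5.3.1 Control group:** "The aim is that each participating hospital gathers a control group which will be compared with their intervention group". Section 5.1.5 likewise has each hospital collect its own controls before the pathway starts there.
- **5.1.5 Sample size:** one overall comparison, "a minimum of 466 patients need to be included, 233 patients in both control and intervention group", with a target of 300 per group. For hospital numbers it adds: "A minimum number of control-patients will be established for each participating hospital, dependent of number of annual patient-visits at the Emergency Department". No matching minimum is given for intervention patients.
- **5.5 Statistical analysis:** "Continuous variables will be analysed using independent t-tests, whereas the categorical data will be analysed by chi-square or Fisher's exact test". Mann-Whitney is listed for non-normal variables. A further sentence says that GEEs will be used to allow for patients of one hospital resembling each other. It mentions neither a hospital term nor a working correlation. "All tests will be performed using a significance level of" 0.05.

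No section says which of these methods decides ED-LOS.

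**The concern.** Section 5.3.1 makes each hospital's own controls the reference for its intervention patients. That is sound, because it keeps differences in ED-LOS between hospitals out of the pathway effect. The advantage survives only if the analysis contrasts patients within hospitals.

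A two-group test on all patients does not do that. If a hospital with long stays supplies a larger share of the controls than of the intervention patients, the pooled difference shows a shorter stay under the pathway even when the pathway does nothing. The reverse mix hides a real effect. Unequal shares are plausible: minimums exist for controls only, the control period may be extended (Protocol 4), and the COVID burden is expected to vary during inclusion. The result on a main endpoint could therefore partly reflect which hospitals recruited when.

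**Working it through.** **1. Reproduce the plan's sample size.** Inputs from 5.1.5: control mean 3 h 20 min = 200 min; reduction of 10% = 20 min; two-sided 0.05; power 80%; SD printed as 1.17 without a unit.

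n per group = 2 × (1.960 + 0.842)² × SD² / 20²

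- SD read as 1 h 17 min = 77 min: n = 232.7, so 233 per group and 466 in total. This matches the plan.
- SD read as 1.17 decimal hours: 194 per group, 388 in total. This does not match.

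SD = 77 min is used below. The calculation is for one comparison of two overall groups.

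**2. What the listed methods estimate.**

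- *t-test:* difference of raw group means, with hospital not used. Mann-Whitney ignores hospital in the same way.
- *GEE with independence working correlation, identity link and treatment as the only covariate:* its estimating equations are those of ordinary least squares, so the estimate equals the same raw difference. Only the standard error changes.
- *GEE with exchangeable correlation:* moves part of the way towards the within-hospital contrast.
- *Model with hospital as a fixed effect:* estimates the within-hospital contrast.

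**3. Size of the hospital-mix bias.** The protocol gives ED-LOS for one hospital only, so the gap and the shift are assumptions. If a share s of patients moves from one hospital to another between the groups, and their mean ED-LOS differs by g:

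bias = g × s

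- g = 40 min, s = 0.10: 4 min, or 4/20 = 20% of the target effect.
- g = 40 min, s = 0.20: 8 min, or 8/20 = 40%.
- Range for g = 20 to 60 min and s = 0.10 to 0.20: 20 × 0.10 = 2 min to 60 × 0.20 = 12 min.

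**4. False-positive rate of a plain pooled test with no pathway effect.** SE = 77 × √(2/n), which is 7.13 min at n = 233 and 6.29 min at n = 300.

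Rate = Φ(−1.96 + bias/SE) + Φ(−1.96 − bias/SE)

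| n per group | bias 4 min | bias 8 min |
|---|---|---|
| 233 | 8.7% | 20.2% |
| 300 | 9.8% | 24.6% |

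**5. Does the GEE repair this?** Simulation with five hospitals, the same 40-minute gap, a shift of 10 to 20 points and no pathway effect:

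- The t-test and the independence GEE were biased by about 4 to 8 min.
- The exchangeable GEE still carried about 3 min at the 20-point shift.
- Both GEE versions rejected the true null in about 14% to somewhat above 20% of runs. Part of this comes from robust standard errors, which are too small with only five clusters.
- The model with a hospital fixed effect had almost no bias and rejected in about 5% of runs.

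**6. Power of a comparison inside one hospital** (20 min, SD 77 min, two-sample t-test, equal hospital sizes assumed):

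| Hospitals | 233 per group overall | 300 per group overall |
|---|---|---|
| 5 | 233/5 ≈ 47 per arm: 24% | 60 per arm: 29% |
| 6 | 233/6 ≈ 39 per arm: 20% | 50 per arm: 25% |

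The same formula gives 80% for the single comparison at 233 per group and 89% at 300.

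**The case against.** The best defence is the GEE sentence in 5.5. The plan does not rest on hospital-blind tests alone. One analysis across hospitals, with each hospital's controls as its reference, would satisfy 5.1.5, 5.3.1 and 5.5 together. The working correlation and hospital terms are details commonly left to an SAP, which is not shown here. The sentence in 5.3.1 sits in a section on how controls are gathered and names no test.

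Much of this stands. A reader might infer that 5.3.1 contradicts the sample size by planning five or six separate hospital tests, with a chance of a false finding of 1 − 0.95⁵ = 22.6% or 1 − 0.95⁶ = 26.5%. The arithmetic is right, but the protocol states neither separate hospital tests nor a rule that any one significant hospital counts as a finding. The figure also counts errors in both directions; for false benefit alone it would be 1 − 0.975⁵ = 11.9% or 1 − 0.975⁶ = 14.1%. None of these is an error rate of the plan as written.

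What the defence does not answer is that 5.5 gives the GEE only a correlation purpose. A GEE that meets that description can return exactly the raw pooled difference, and 5.5 also keeps the unadjusted two-group tests for continuous variables. An SAP could follow 5.5 faithfully and still miss the contrast in 5.3.1.

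It is also fair that the gap and the shift are assumed. Controls-only minimums show that the shares can differ, not that they will.

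**Conclusion.** The concern holds as a mismatch between the intended comparison and the methods listed for it. It is not a demonstrated contradiction and not a multiplicity failure. Sections 5.3.1 and 5.1.5 are compatible if each hospital's controls serve as its reference inside one overall analysis, but 5.5 does not secure that analysis.

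Under the assumed 40-minute gap and 10 to 20 point shift, a null pathway would appear to change ED-LOS by 4 to 8 minutes, and a plain pooled test would be falsely significant in about 9 to 25% of trials. If hospital shares are equal in the two groups, or hospitals have the same mean ED-LOS, this bias vanishes. The small-cluster problem of the GEE standard errors does not. Hospital-level significance claims would have only about 20 to 29% power each, so they should not carry conclusions. The change is worth making before analysis.

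**What to change.** **In 5.5:** state that ED-LOS is decided by one pathway-versus-control effect, estimated from a single model across all hospitals with hospital as a fixed (categorical) effect and tested once at two-sided 0.05. This takes the place of the unadjusted two-group test for this endpoint.

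**In 5.3.1:** state that a hospital's own controls are its reference within that model, and that hospital-specific differences are shown descriptively as estimates with 95% confidence intervals, without significance claims.

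**Cost:** a few sentences and no new data, since the hospital of every patient is known. Hospitals give up their own significance claims, which their numbers could not support. Hospital adjustment also leaves one problem open. Controls precede the pathway within each hospital, the design is described as stepped-wedge, and Protocol 4 expects COVID-related changes in care over the same period. The deciding model must deal with calendar time separately, and the text should say so.

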## 5.4 STUDY PARAMETERS / ENDPOINTS

### 5.4.1 Main study parameter/endpoint

#### *Baseline characteristics:*

- Age in years
- Gender (male/female)
- Referral category NSC
  - o Somatic
  - o Higher demand of care
  - o Cognitive problems
  - o Functional status
  - o Unexplained falls
- Main diagnosis at ED (DOT/DBC/ICD10)
- Way of arrival (per ambulance, public transportation, own transport, etc.)
- APOP-score
- Adherence to the recommended actions after APOP-screening and risk of functional decline
- Specialist seeing the patient and consulting specialists during ED-stay
- Diagnostic tests (X-ray, EKG, urinalysis, bladder scan and the frailty lab)
- ED-logistics (time of arrival at ED, duration of triage, triage colour, ED loss etc)
- In the case of admission: duration of admission (days) and reason for admission
- Living situation (independent, care at home, etc)
- Zip (postal code)
- Discharge destination (home, facility, care at home)
- Change in medication list after review
- Patient satisfaction

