## 1. SUMMARY

**Rationale:** Approximately, 10-20% of older adult patients present with non-specific complaints (NSCs) at the emergency department (ED). NSCs are known as poorly described symptoms, such as 'weakness' and 'fatigue', often leading to an extensive differential diagnosis. Almost half of patients presenting with NSCs suffer from a serious underlying illness. Currently, a management protocol for patients with NSCs does not exist. Patients with NSCs are often under triaged, stay longer at the ED (ED-LOS) or hospital (HOSP-LOS) and are at a higher risk for complications during hospitalisation. A special care pathway for patients with NSCs was designed to resolve some of these problems and improve the efficiency of care at the ED.

**Objective:** To implement and evaluate a care pathway for older adults presenting with non-specific complaints at the emergency department.

**Study design:** A longitudinal multi-centre cohort with a stepped-wedge cluster design.

**Study population:** Older adults  $\geq 70$  years of age presenting with NSCs at the practice of the general practitioner (GP), the elderly care physician at a nursing home or the emergency department of the hospital will be evaluated for inclusion. Data from control patients will be collected retrospectively.

**Recruitment:** Recruitment will take place during workdays between Monday – Friday from 11:00 am – 20:00 pm and comprise of a study period of 6 months, according to the study protocol. The primary health care provider (such as a GP or elderly care physician at a nursing home) will indicate whether a patient is eligible for access to the care pathway and inform the specialist at the ED. Every referring care professional will have a card, which provides information on how to refer a patient to the care pathway and to whom. Patients can also enter the care pathway after triage at the ED, if the main complaint is non-specific. If the ED specialist registers access to the care pathway and the patient gives consent, the patient will be included and baseline data collected.

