## **4. METHODS**

### **STUDY DESIGN**

The following organizations will implement the care pathway:

- Catharina Ziekenhuis, Eindhoven, the Netherlands
- ETZ (Elisabeth-TweeSteden Ziekenhuis), Tilburg, the Netherlands
- Jeroen Bosch Ziekenhuis, 's Hertogenbosch, the Netherlands
- Maxima Medisch Centrum, Veldhoven, the Netherlands
- St. Anna ziekenhuis, Geldrop, the Netherlands
- General practitioners of the Brabant area
- Nursing homes

Optional hospitals:

- Amphia, Breda, the Netherlands

Inclusion will take place during approximately 6 months after initiation of the study on workdays between Monday – Friday from 11:00 am – 20:00 pm.

The first hospitals were planned to initiate the study and start implementation of the care pathway and data collection in December 2019 or at the earliest possibility after approval of the study protocol. Due to the COVID-pandemic and its burden on hospital-care throughout the Netherlands, implementation could not take place as planned. The Jeroen Bosch Hospital had started the care-pathway, but had to discontinue after a few weeks due to the massive burden of COVID-care.

Considering that the COVID-pandemic, which resulted in a drop of regular care, may have had an influence on the processes in the ED and the number of elderly people presenting with non-specific complaints, it was decided to temporarily withhold the inclusion of control patients and implementation of the care-pathway. The estimation was made that the COVID-pandemic would be a great confounder in results when comparing a pre-pandemic and post-pandemic population. Therefore it was decided to start over with inclusion of the control-group. In July and August 2020 the participating hospitals were consulted and asked if they had resumed their usual care and how their ED and population had changed. All hospitals agreed to restart inclusion of the control-group from August 2020 onward. Since the numbers of elderly people with non-specific complaints are

expected to be lower than before the COVID-pandemic, it is possible that the period for inclusion for the control group has to be extended. The planned start for implementation of the care-pathway is January 2021, dependent on inclusion of the control-group and the evolution of the COVID-pandemic.

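### The before-after comparison of ED length of stay has no patient-level adjustment in Section 5.5, and the baseline list in Section 5.4.1 mixes pre-pathway variables with pathway processes and endpoints

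*Protocol*

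**What the plan says.** The Summary labels the study "A longitudinal multi-centre cohort with a stepped-wedge cluster design". Section 5.1.5 states: "Each hospital will gather their own control-group before implementation of the care-pathway". Section 5.3.1 adds: "The aim is that each participating hospital gathers a control group which will be compared with their intervention group". No randomisation of patients, hospitals or start dates is described.

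The groups enter differently. Under Section 5.1.4, controls meet the same eligibility criteria but are not individually asked for consent. They come from a CTcue search of the records or, where CTcue is unavailable, from patient numbers saved by the ED specialist. Pathway patients give consent (Summary), can be excluded for refusing (Section 5.1.3), and may arrive through a GP or nursing-home referral supported by an information card (Section 5.1.1).

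On analysis, Section 5.5 says: "Continuous variables will be analysed using independent t-tests". Categorical data go to chi-square or Fisher's exact tests, and non-normal data to the Mann-Whitney test. GEE is to be used, and its stated purpose is the similarity of observations within a hospital. No patient covariate is named.

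Under the baseline heading, Section 5.4.1 lists age, gender, referral category, way of arrival and living situation. The same list contains "Adherence to the recommended actions after APOP-screening and risk of functional decline", "In the case of admission: duration of admission (days) and reason for admission", "Diagnostic tests (X-ray, EKG, urinalysis, bladder scan and the frailty lab)", the specialists seen and consulted, discharge destination, medication change after review, and patient satisfaction.

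**The concern.** A t-test of ED-LOS between two calendar periods reads every difference between the periods as an effect of the pathway. Here the periods can differ in who is counted. A record search captures patients whether or not they would have agreed to take part, whereas the pathway group depends on a clinician recognising the complaint, on referral and on consent. Allowing for hospital clustering corrects the standard error; it does not remove a difference in case mix within a hospital.

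The obvious remedy is covariate adjustment, and the protocol's only list headed as baseline is in Section 5.4.1. Several of its entries arise after the pathway has begun to act, and some are endpoints. A baseline table built from it would show effects of the pathway as group imbalance. A covariate set taken from it would condition on consequences of the intervention.

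**Working it through.** **1. The plan's own figure.** From Section 5.1.5: mean ED-LOS 3 h 20 min = 200 min; reduction 10%, so the target is 0.10 × 200 = 20 min; two-sided α = 0.05; power 80%; SD printed as 1.17.

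Formula: n per group = 2 × (1.960 + 0.842)² × (SD / 20)².

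- SD read as 1 h 17 min = 77 min: 232.7, so 233 per group and 466 in total. This reproduces the plan.
- SD read as 1.17 h = 70.2 min: 193.4, so 194 per group and 388 in total. This does not.

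The 466 is therefore the size for a simple unadjusted comparison of two means. I use 77 min below.

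**2. What a residual shift does.** Assume no true effect, and let uncorrected case mix shift mean ED-LOS by b minutes. Then SE = 77 × √(2/n), which is 7.13 min at n = 233 and 6.29 min at n = 300 (the recruitment target). The two-sided rejection rate is Φ(b/SE − 1.96) + Φ(−b/SE − 1.96).

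| Assumed shift b | Share of 20 min | 233 per group | 300 per group |
|---|---|---|---|
| 0 min | 0% | 5% | 5% |
| 4 min | 20% | 8.7% | 9.8% |
| 5 min | 25% | 10.8% | 12.5% |
| 10 min | 50% | 28.9% | 35.6% |

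Worked line: b = 4, n = 233 gives 4/7.13 = 0.561, and Φ(−1.399) + Φ(−2.521) = 0.081 + 0.006 = 0.087.

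A shift of b is the imbalance in a binary factor multiplied by its effect on ED-LOS. A 10-point imbalance with a 40-minute effect gives 4 min. Imbalances of 5 to 20 points with effects of 30 to 90 min give 1.5 to 18 min. All of these are assumptions; the protocol gives no such figures.

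**3. The Section 5.4.1 list against the rest of the protocol.**

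| Item listed as baseline | Its role elsewhere |
|---|---|
| Patient satisfaction | Primary objective (Section 3); measured on leaving the pathway (Section 5.2) |
| Duration of admission | Endpoint HOSP-LOS (Section 5.4.1) |
| Discharge destination | Secondary objective (Section 3) |
| Diagnostic tests | Their quantity is an endpoint (Section 5.4.1); a standard set is part of the pathway (Section 5.3) |
| Adherence to APOP actions | Follows from the pathway's screening step (Section 5.3) |
| Medication change after review | Result of the pathway's medication review (Section 5.3) |
| Specialists seen and consulted | Seniority of the treating doctor is part of the pathway (Section 5.3) |

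**4. If such items were used as covariates.** Suppose the true effect is 20 min and half of it runs through them. The adjusted model then targets 10 min, and power falls from 80% to about 29% at 233 per group, or from 89% to about 36% at 300. This is one direction only. If the standard test set lengthens the stay, adjusting for tests would enlarge the apparent benefit.

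**The case against.** **Covariates belong in the SAP, and GEE can carry them.** A missing covariate list would indeed not be a finding, and nothing in Section 5.5 forbids covariates. But Section 5.5 names unadjusted tests for a contrast that is not randomised, and gives GEE a single purpose. Followed as written, the plan leaves case mix in the estimate. That part stands.

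**Nobody plans to adjust for the Section 5.4.1 list.** Correct. The list sits among study parameters and works as a data-collection list; the Summary calls many of the same items study parameters. A reader might infer that the trial will over-adjust and so bias the result towards no effect. The text supports neither the plan nor the direction.

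**COVID.** A reader might take "The estimation was made that the COVID-pandemic would be a great confounder in results when comparing a pre-pandemic and post-pandemic population" as the protocol's admission that its two groups will differ. It is not. The sentence concerns populations before and after the pandemic, and the response was to restart the controls, from August 2020, ahead of a pathway start planned for January 2021. The Study Design section also plans to monitor organisational change in each ED. It predicts no case-mix shift between the two study groups.

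**APOP score.** A reader might conclude that controls have none, so that adjusting for it would drop them all. The protocol does not say so. The score belongs to the pathway's screening, but Section 5.1.4 says control data are retrieved according to the study parameters, of which the score is one.

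**Adjustment has limits.** It cannot remove unmeasured differences. The referral card might itself alter way of arrival. A calendar-time term is inseparable from the intervention if all hospitals start together, and the current text gives one planned start. These points stand and shape the fix.

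**Conclusion.** The point holds, and the plan should be changed. The primary ED-LOS contrast is before-after within hospitals, the routes into the two groups differ, and the named tests do not adjust for patient characteristics. The baseline list also places pathway processes and endpoints, including a primary objective, beside true baseline values.

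The amount of bias cannot be derived from the documents. With an SD of 77 min and a 20-minute target, a 4-minute residual shift would give a false-positive rate of about 9% at 233 per group, and a 10-minute shift about 29%. These figures show how sensitive the test is; they do not forecast the bias. The harm from adjusting for post-arrival items is conditional on their being used, and its direction is open.

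**What to change.** In Section 5.5, make the primary ED-LOS analysis the GEE already planned (or a regression with hospital terms), adjusted for prespecified pre-pathway variables: age, gender, NSC referral category, way of arrival, living situation and time of arrival. Keep the unadjusted test as secondary. Add a calendar-time term only if hospitals start the pathway on different dates.

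In Section 5.4.1, split the list into pre-pathway characteristics and process or outcome items. State that the second group is not used for adjustment, and that the APOP score is not either if it is not recorded for controls.

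All the proposed covariates are already on the collection list. The cost is some wording, a few model terms, and possibly missing covariate values in controls collected retrospectively, for which a rule should be set in advance.
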